#### Subtypes of AMI assessed in subgroup analyses will be:

Occlusive arterial AMIThrombosisEmbolismUnclearMesenteric venous thrombosisNOMI

Patients with suspicion of AMI will be identified by treating physicians who inform study investigators. Study inclusion, confirmation and subtype of AMI will be validated by at least one study investigator. Principal investigator at each site is responsible for building up the study team and logistics as best suitable for local conditions.

In case the mechanism of AMI remains unclear or there is another specific mechanism (e.g. dissection, aneurysm, abdominal compartment syndrome), this case will be discussed in steering committee and allocated to the most suitable category and mentioned respectively in the final report.

### Study period and sites

We will invite sites participating in the AMESI study [3] and in the GUTPHOS study (NCT05909722) and open the study for other interested sites, while limiting participation to sites located within a distance range from Tartu, Estonia that allows safe shipment of frozen samples. There is no limitation for the category of the hospital, but we aim to recruit acute care hospitals commonly encountering at least one patient with AMI per month. Each site is expected to include at least 8 patients (in total for suspected and confirmed AMI) within the first 4 months of the study, until the interim analysis, and at least 20 patients in total. The study will start in October 2024 the earliest, with planned recruitment for 8–10 months, whereas the total length of the study period will be defined after the interim analysis at four months after the study start.

### Study procedures

Decisions regarding diagnostics and treatment in study patients will not be influenced by the study, the only study procedure is additional blood sampling.

#### List of biomarkers

The following biomarkers potentially identifying AMI will be centrally measured in Tartu, Estonia: intestinal fatty acid-binding protein (I-FABP), alpha-glutathione S-transferase (Alpha- GST), interleukin 6 (IL-6; LOINC# 26881–3), procalcitonin (PCT; LOINC# 75241–0), ischaemia-modified albumin (IMA; LOINC# 75239–4), D-lactate (LOINC# 14045–9), signal peptide-CUB-EGF domain-containing protein 1 (SCUBE-1), lipopolysaccaharide-binding protein (LBP; LOINC# 88054–2), D-dimers (LOINC# 48065–7). Logical Observation Identifiers Names and Codes (LOINC) is a universal standard database for identifying medical laboratory observations [12].

The list will be kept open for late changes if any novel biomarker emerges before the first laboratory analyses are performed, provided that this marker is possible to measure without an additional sampling tube.

Additionally to centrally measured biomarkers the sites will be asked to measure the following at local hospital laboratories:Blood lactate (arterial, where available), pH, bicarbonate and base excess at each of the planned time points as appropriate for each particular patient.Creatinine (LOINC # 14682–9), high sensitive Troponin T (LOINC # 89576–3) or Troponin I (LOINC # 89577–1), white blood cell count (WBC, LOINC # 6690–2) and C-reactive protein (CRP, LOINC# 1988–5) at time points 1, 2 and 6.

#### Blood sampling time points

Two sampling tubes (one serum and one plasma, arterial or venous) will be collected at each measurement point, allowing central measurement of aforementioned biomarkers.

Depending on whether AMI is confirmed or not, and on treatment methods applied, different measurement time points will apply for each patient (Table 1 and Fig. 1).

**Table 1 Tab1:** Sampling time points for biomarkers measurements (M)

M no	Time point for blood sampling	Confirmed AMI with intervention	Suspicion of AMI*	Confirmed AMI without intervention
M1	Admission (suspicion, if in-hospital)	x	x	x
M2	6-8 h after the first sample if no intervention performed by then	x (if no intervention before 6-8 h)	x	x
M3	At intervention	x (incl. i/a vasodilation)		
M4	4–6 h after intervention	x		
M5	12 h after intervention	x		
M6	24 h after the first sample if no intervention		x (if suspicion still actual)	x
M7	At the time of re-intervention	x (if any within 72 h)		
M8	48 h after the first sample		x (if suspicion still actual)	x (if no intervention)

* If the case is confirmed, the patient will be moved to either column “Confirmed AMI with intervention” or “Confirmed AMI without intervention”

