#### Confirmed AMI will be defined as:

Total or subtotal occlusion of any large mesenteric vessel visualized on CT, magnetic resonance imaging (MRI) or plain angiography with acute symptoms (e.g. abdominal pain, diarrhoea, shock, mucosal sloughing).Imaging finding without any symptoms of intestinal ischaemia and without any laboratory abnormalities is not sufficient to confirm AMI (probably indicating chronic mesenteric ischaemia). For definitive confirmation in such case either endoscopic finding of mucosal ischaemia, surgical finding of transmural ischaemia leading to resection or palliation, or autopsy finding of any stage of bowel ischaemia is needed to confirm the diagnosis.Non-occlusive mesenteric ischaemia confirmed by either endoscopy, surgery or autopsy. A suspicion of NOMI in CT, MRI or angiography without being confirmed by any of these methods remains a suspicion of AMI.

Each case without definitive confirmation of AMI or without definitive confirmation of the subtype of AMI will be carefully reviewed by steering committee members and discussed with respective site to confirm the final categorization.

Patients with strangulating bowel obstruction (SBO) as an immediate verified diagnosis at the time of the first clinical assessment will be excluded from this study. If a SBO was identified as a cause of AMI only after including the patient in the study (as suspected AMI), this patient should continue in the study.

Patients with acute-on-chronic mesenteric ischaemia will be included.

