Statistical analysis will be performed with R Statistical Software 4.3.2 (R Core Team, Vienna, Austria, 2023). Data will be described in number (%), median (interquartile range, IQR) or mean (standard deviation, SD) as appropriate. Kolmogorov–Smirnov test will be used for data distribution normality testing. Analyses for confirmed transmural AMI vs suspected but not confirmed AMI (comparison A – primary outcome), confirmed AMI of any stage vs suspected but not confirmed AMI (comparison B – secondary outcome) and transmural vs non-transmural AMI (comparison C – secondary outcome) will be performed in different measurement time points. Each biomarker will be described at each measurement point for all comparisons (A, B and C), using Student’s t-test or Wilcoxon rank-sum test as appropriate. For all biomarkers showing a *p*-value < 0.05 in at least one measurement point in univariate analysis, the area under the receiver operating curve (ROC) calculation will be performed. We will do this separately for comparisons A, B and C and identify optimal cut-off values for each biomarker based on maximum value of the Youden index [13]. All measurement time points before any treatment of AMI (1,2,3,6,8) will be pooled and AUROC analysis will be performed to identify the best cut-offs also for pooled data for each biomarker. Sensitivity, specificity, positive predictive value (PPV), negative predictive value (NPV) and likelihood ratios (LR) with 95% CI-s will be reported. Positive likelihood ratio (LR +) > 10 and negative likelihood ratio (LR-) < 0.1 will be considered high diagnostic accuracy and LR +  > 5 and LR- < 0.2 as moderate diagnostic accuracy. All biomarkers with at least moderate accuracy will be entered as binary covariates (using the best cut-offs previously found in the AUROC analyses resulting in highest AUC) into the multivariable stepwise logistic regression analysis (both directions) to identify the best combination of biomarkers discriminating between transmural AMI and no AMI based on Akaike information criterion (AIC). Analogical approach will be used for comparisons B and C. The best models will be applied to subgroup analyses in different sub-types of AMI. If the best models selected as described previously, do not perform well at different measurement time points or in different subtypes of AMI, additional analyses will be undertaken testing alternative combinations. We will present the best models for each comparison and for each subtype separately and will use them to construct a practical score that can be used to distinguish between no AMI, non-transmural AMI and transmural AMI (Table 3). If the different cut-offs from different models contradict (for example cut-off for non-transmural AMI vs transmural AMI is lower than the cutoff for no AMI vs AMI) additional analyses will be performed and more appropriate cut-offs will be found considering acceptable sensitivity and specificity from previous AUROC analyses. This approach will be compared to decision tree approach and if the decision tree accuracy is higher than the score’s accuracy, a decision tree will be preferred. The accuracy of the decision tree and the score will be calculated as proportion of correct predictions.

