
**Table 3 Tab3:** Hypothetical visualization of a practical score for diagnosis of AMI

	No AMI	Non-transmural AMI	Transmural AMI
Biomarker 1	< x = 0 points	x–y = 1 point	> y = 2 points
Biomarker 2	< x = 0 points		> x = 2 points
Biomarker 3	< x = 0 points	x–y = 1 point	> y = 2 points
Biomarker 4	< x = 0 points	> x = 1 point	
Biomarker 5	< x = 0 points		> x = 2 points

This visualization is hypothetical. PPV – positive predictive value

Hypothetical examples: 0–1 points = no AMI (PPV; 2–4 points = non-transmural AMI (PPV); > 5 points = transmural AMI (PPV)

Dynamics of each biomarker will be visualized graphically in patients with confirmed AMI differentiating between patients in whom initial treatment was successful from patients in whom bowel ischaemia was ongoing after initial treatment, with the aim to explore possible differences in biomarker trajectories in case of reperfusion and ongoing bowel ischaemia.

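### Intervention sampling is tied to confirmed AMI, so a patient vasodilated for still-unconfirmed NOMI has no intervention samples scheduled, and a post-treatment 48 h value can be pooled as pre-treatment

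*Protocol article*

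**What the plan says.** Table 1 (Blood sampling time points) has three columns: confirmed AMI with intervention, suspicion of AMI, and confirmed AMI without intervention. The text introduces it with "Depending on whether AMI is confirmed or not, and on treatment methods applied, different measurement time points will apply for each patient".

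- **Intervention samples.** M3, M4, M5 and M7 are marked only in the first column. The M3 cell is "x (incl. i/a vasodilation". The suspicion column has M1, M2, M6 and M8.
- **Changing column.** The footnote says "If the case is confirmed, the patient will be moved to either column" for confirmed AMI with or without intervention. It gives no other route.
- **Confirming NOMI.** The definition of confirmed AMI accepts "Non-occlusive mesenteric ischaemia confirmed by either endoscopy, surgery or autopsy" and adds "A suspicion of NOMI in CT, MRI or angiography without being confirmed by any of these methods remains a suspicion of AMI".
- **Case review.** "Each case without definitive confirmation of AMI or without definitive confirmation of the subtype of AMI will be carefully reviewed by steering committee members", who settle the final category with the site.
- **Analysis.** Comparisons A and B use suspected but unconfirmed AMI as the comparator. For cut-offs, "All measurement time points before any treatment of AMI (1,2,3,6,8) will be pooled". For the tertiary objective on biomarker patterns, "Dynamics of each biomarker will be visualized graphically in patients with confirmed AMI differentiating between patients in whom initial treatment was successful" from those whose ischaemia continued.
- **Abstract, Methods.** Blood is taken on admission and around interventions, or over the first 48 h of suspicion where there was no intervention. Here the dividing line is the intervention, not confirmation.

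**The concern.** A NOMI patient can receive intra-arterial vasodilation on angiographic findings alone. Table 1 names that treatment as an intervention, but the definitions keep the patient in a column without intervention sampling. The parts of the protocol do not fit together for this patient, and a site following Table 1 would not draw the samples.

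Three things are at stake. Samples not drawn cannot be recovered at analysis. A patient who may truly have had NOMI is counted as a non-case in comparisons A and B and is absent from the trajectory display. And because surgery and autopsy are more likely after treatment failure, the final label can depend partly on the response to treatment. In addition, the M8 cell for suspected AMI allows a 48 h sample after treatment to reach the pooled pre-treatment analysis.

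**Working it through.** **Step 1. Follow one patient.** Suppose NOMI is seen at angiography, vasodilation is given, and there is no endoscopy, surgery or autopsy by then.

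| Table 1 row | Confirmed, with intervention | Suspicion (where this patient sits) |
|---|---|---|
| M3 | due, vasodilation named | blank |
| M4 | due | blank |
| M5 | due | blank |
| M7 | due if re-intervention within 72 h | blank |
| M6 | blank | due only without intervention (row label) |
| M8 | blank | due if AMI is still suspected, with no condition on intervention |

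None of the four intervention rows applies to this patient. The Fig. 1 legend does not settle the case: Patients 1 and 2 are treated for AMI, Patient 3 has no intervention, and no example is treated but unconfirmed.

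**Step 2. The final label.** Three routes confirm NOMI. Endoscopy does not depend on treatment failing. Surgery and autopsy are more likely when it does. A responder without endoscopy stays unconfirmed unless the steering committee review changes the category, while a failure who reaches surgery or autopsy can be confirmed. The label can therefore vary with outcome. Sampling does not clearly do so: a failure confirmed only at later surgery was also unconfirmed at vasodilation, and on the same literal reading had no M3 due then.

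**Step 3. M8 and pooling.** M2 and M6 carry a no-intervention condition in their row labels. M8 carries one only in the cell for confirmed AMI without intervention. The Statistical analysis section lists M8 by number among the pre-treatment points, so a suspected patient vasodilated before 48 h can supply a post-treatment value. M6 is protected by its row label.

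**Step 4. Would a few such patients matter?** The plan has 160 confirmed AMI (40 with NOMI) and 90 unconfirmed, and 160 + 90 = 250, as stated. The target for comparison B is a positive likelihood ratio (LR+) above 10. The documents give no number of vasodilated or unconfirmed true NOMI, so what follows is an assumed illustration.

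Let k patients with true NOMI move from the confirmed group to the comparator, and assume they test positive as often as confirmed cases. Then:

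- share of comparator that is true NOMI: q = k / (90 + k)
- observed specificity = (1 − q) × spec + q × (1 − sens)
- observed LR+ = sens / (1 − observed specificity)

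| k | q | Observed spec (true 0.92/0.92) | LR+ (0.92/0.92) | LR+ (0.95/0.95) |
|---|---|---|---|---|
| 0 | 0% | 0.920 | 11.5 | 19.0 |
| 2 | 2.2% | 0.902 | 9.4 | 13.7 |
| 5 | 5.3% | 0.876 | 7.4 | 9.8 |
| 10 | 10.0% | 0.836 | 5.6 | 6.8 |
| 20 | 18.2% | 0.767 | 4.0 | 4.5 |

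For k = 5 and 0.92/0.92: (90/95) × 0.92 + (5/95) × 0.08 = 0.876, and 0.92 / 0.124 = 7.4. If the k patients are instead counted within the planned 90, specificity is 0.92 − 0.84 × 5/90 = 0.873 and LR+ is 0.92 / 0.1267 = 7.3, so the choice of denominator changes little.

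This arithmetic applies to any true NOMI left unconfirmed. Vasodilated patients are only part of that group.

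**The case against.** The strongest reply is that the protocol already says what is wanted. The Abstract splits sampling by intervention, the text before Table 1 makes the schedule depend on treatment methods as well as confirmation, and the treated patients in Fig. 1 have M3 to M5. This shows the intention. But Table 1 is the instruction that sites follow, its suspicion column is blank, and its footnote moves patients on confirmation only.

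A second reply is that the vasodilation entry is valid as it stands, because it can apply to an imaged occlusion or to NOMI already confirmed by endoscopy. That is right. The cell is not void, and the gap concerns only patients treated while unconfirmed.

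A third is that the qualifier in the pooling sentence itself excludes post-treatment values, and that the Abstract limits 48 h sampling to patients without intervention. An analyst applying the qualifier would drop the value. One selecting by the listed time point numbers would keep it.

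A reader might infer that all successfully vasodilated NOMI patients drop out, or that responders lose M3 to M5 while failures keep theirs. The documents support neither: endoscopy can confirm a responder, committee review may alter the category, and late-confirmed failures lack the same samples. Committee review cannot, however, restore samples never drawn.

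It is also fair that the trajectory display is a descriptive, tertiary analysis, and that requiring endoscopy, surgery or autopsy for NOMI is a deliberate strict standard. That standard is not disputed here.

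**Conclusion.** The point holds for a defined group: patients given a treatment intervention, notably intra-arterial vasodilation, while AMI is still unconfirmed. For them Table 1 schedules none of M3, M4, M5 or M7, contrary to the Abstract. Those who remain unconfirmed enter the comparator of A and B and leave the trajectory display. The M8 cell separately permits a post-treatment value in the pooled cut-off analysis.

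That the final label depends partly on outcome is plausible, resting on the assumption that surgery and autopsy are more likely after failure. Its size cannot be estimated, because the documents give no number vasodilated, no response share and no endoscopy rate. A reader might go further and infer that the group with successful initial treatment would be all but empty for vasodilated NOMI. That would need no responder to have endoscopy and no case to be reclassified, which the documents do not say. The likelihood ratio figures show only that small counts could matter near the LR+ target, under the stated assumptions.

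This should be corrected, because undrawn samples are lost for good. It does not undermine the design as a whole.

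**What to change.** Reconcile Table 1 with the Abstract, the definition of confirmed AMI and the pooling sentence:

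1. Let the sampling schedule follow the intervention. Any enrolled patient given a treatment intervention for suspected AMI has M3, M4 and M5, and M7 where it applies, whatever the confirmation status at that moment.
2. Add to the M8 suspicion cell the no-intervention condition that the M6 row already carries.
3. State in the Statistical analysis section that any sample taken after a treatment intervention is excluded from the pooled pre-treatment analysis, whatever its time point number.
4. Flag treated but unconfirmed NOMI in the database, and run comparisons A and B and the trajectory display with and without these patients.

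The cost is a few lines of wording, one database flag and up to four extra sampling points in a small number of patients. Such a patient would have at most M1, M2, M3, M4, M5 and M7. That is what Table 1 already allows for confirmed AMI with intervention, so the stated 96 mL maximum is not affected. The confirmation standard, diagnostic work-up and treatment stay as they are.

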**Methods:**

This is a prospective multicentre study. Adult patients with clinical suspicion of AMI (*n* = 250) will be included. Blood will be sampled on admission, at and after interventions, or during the first 48 h of suspicion of AMI if no intervention undertaken. Samples will be collected and the following serum or plasma biomarkers measured at Tartu University Hospital laboratory: intestinal fatty acid-binding protein (I-FABP), alpha-glutathione S-transferase (Alpha- GST), interleukin 6 (IL-6), procalcitonin (PCT), ischaemia-modified albumin (IMA), D-lactate, D-dimer, signal peptide-CUB-EGF domain-containing protein 1 (SCUBE-1) and lipopolysaccharide-binding protein (LBP). Additionally, more common laboratory markers will be measured in routine clinical practice at study sites.

Diagnosis of AMI will be confirmed by computed tomography angiography, surgery, endoscopy or autopsy.

Student’s t or Wilcoxon rank tests will be used for comparisons between transmural vs. suspected (but not confirmed) AMI (comparison A), confirmed AMI of any stage vs suspected AMI (comparison B) and non-transmural AMI vs transmural AMI (comparison C). Optimal cut-off values for each comparison will be identified based on the AUROC analysis and likelihood ratios calculated. Positive likelihood ratio > 10 (> 5) and negative likelihood ratio < 0.1 (< 0.2) indicate high (moderate) diagnostic accuracy, respectively. All biomarkers with at least moderate accuracy will be entered as binary covariates (using the best cutoffs) into the multivariable stepwise regression analysis to identify the best combination of biomarkers for all comparisons separately. The best models for each comparison will be used to construct a practical score to distinguish between no AMI, non-transmural AMI and transmural AMI.

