## Methods

### Objectives

#### Primary objective:

To identify a combination of biomarkers that distinguishes patients with transmural AMI from patients with no AMI with a positive likelihood ratio of > 10 and negative likelihood ratio of < 0.1 at least at one measurement time point before any treatment of AMI (comparison A).

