**Inflammatory markers**			
IL-6	Inflammatory marker (not tissue-specific)	Plasma: LH-tube Amount: 0.2 mL Method: Cobas ECLIA; Provider: Roche Diagnostics, Germany) Reference value: < 7 ng/L	Moderate accuracy in humans (4). Animals: fast peak (6 h), increase with reperfusion; IVD-R compatible
PCT	Inflammatory marker (not tissue-specific)	Plasma: LH-tube Amount: 0.2 mL Method: Cobas ECLIA; Provider: Roche Diagnostics, Germany) Reference value: < 0,5 µg/L	Moderate accuracy in humans (4); IVD-R compatible

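### M3 is pooled as a pre-treatment sample, but the schedule does not require it to be drawn before the procedure starts and leaves it blank for patients still only suspected of AMI

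*Protocol article*

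**What the plan says.** The primary objective (Objectives) asks for the target likelihood ratios "at least at one measurement time point before any treatment of AMI (comparison A"); both secondary objectives carry the same restriction. The Statistical analysis section lists the samples taken to satisfy it: "All measurement time points before any treatment of AMI (1,2,3,6,8) will be pooled". Cut-offs for each biomarker are then sought in the pooled data as well as at single time points.

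Table 1 (Blood sampling time points) gives the timing of M3 as "At intervention". Its only entry is under confirmed AMI with intervention, and reads "x (incl. i/a vasodilation"). The cells for suspected AMI and for confirmed AMI without intervention are empty. The footnote to the suspicion column says: "If the case is confirmed, the patient will be moved to either column". The Fig. 1 legend repeats the same timing for M3 and adds no rule about the order of draw and procedure.

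The abstract accepts several routes to confirmation: "Diagnosis of AMI will be confirmed by computed tomography angiography, surgery, endoscopy or autopsy". The Definitions section narrows this for one subtype: "Non-occlusive mesenteric ischaemia confirmed by either endoscopy, surgery or autopsy". NOMI suspected on imaging alone stays in the suspected category.

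**The concern.** Two gaps meet at M3.

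The first is timing. Whether M3 precedes treatment decides whether it belongs in the pool, yet the schedule fixes only that it coincides with the procedure. Blood taken after the procedure has begun, or after flow is restored, fits the label. The protocol itself treats reperfusion as something that changes the markers. The Background criticises earlier studies for ignoring it, a tertiary objective separates reperfusion from ongoing ischaemia, and the IL-6 entry in Table 2 reads "Animals: fast peak (6 h), increase with reperfusion". Table 2 reports a rise with reperfusion for D-lactate too, and a small one for SCUBE-1. Post-reperfusion values inside the pre-treatment pool would mix the two states that the study sets out to separate, and would feed into the cut-offs.

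The second is who is sampled. A patient who goes to a procedure while AMI is only suspected sits in a column with no M3. If the procedure supplies the confirmation, the instruction to draw M3 arrives only then. A sample that was drawn late or not drawn cannot be recovered in analysis.

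**Working it through.** No sample-size or power figure depends on this point, so the check sets the schedule against the analysis set.

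**Step 1: pre-treatment samples by column.** The analysis set is {1, 2, 3, 6, 8}. Intersecting it with each column of Table 1:

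| Table 1 column | Scheduled | In the pre-treatment set | M3 due? |
|---|---|---|---|
| Confirmed, with intervention | 1, 2, 3, 4, 5, 7 | 1, 2, 3 | yes |
| Suspected | 1, 2, 6, 8 | 1, 2, 6, 8 | no |
| Confirmed, no intervention | 1, 2, 6, 8 | 1, 2, 6, 8 | no |

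M3 is due in one column of three.

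**Step 2: is there a before-start condition?** M2 and M6 are each tied in Table 1 to no intervention having taken place, and M8 carries the same condition for confirmed cases without intervention. M4 and M5 are timed after the intervention. M3 has no condition in either direction, and the Fig. 1 legend supplies none. This gap applies to every patient with an M3, including those whose occlusion was already confirmed on imaging.

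**Step 3: who enters the procedure without an M3 due?** Occlusive AMI seen on imaging with acute symptoms is confirmed beforehand, so these patients are already in the right column. NOMI cannot be confirmed by imaging. A NOMI patient not yet confirmed by endoscopy is therefore still in the suspicion column at the start of an operation, as is an occlusive case that surgery is the first to confirm.

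**Step 4: how many?** The Sample size section plans 250 patients: 160 confirmed, of whom 40 have NOMI, and 90 not confirmed (160 + 90 = 250). NOMI is 40/160 = 25% of confirmed cases, but that is a ceiling for the NOMI part, not an estimate. Endoscopy or autopsy can also confirm NOMI, and some patients have no intervention. The affected NOMI number is anywhere from 0 to 40. Occlusive cases first confirmed at surgery add a number that the article does not give.

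**Step 5: what is left if M3 is late or missing?** M1 is scheduled in every column, and M2 is added if no intervention has occurred by 6–8 h. The loss is the latest pre-treatment value, not all pre-treatment values.

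**The case against.** The strongest reply is that the intention is clear. The abstract ties sampling to the intervention rather than to confirmation: blood is taken on admission and both at and after interventions. On that rule a suspected patient going to a procedure is sampled at it. The columns of Table 1 can then be read as final categories, to which the footnote reassigns the patient. The table also contrasts M3 with M4 and M5, which come after, and the analysis section expressly classes M3 as pre-treatment. Confirmation on opening the abdomen need not mean that treatment has begun, since a sample could still precede resection or revascularisation. The article is a condensed document, and the case report form in Additional File 1, which is not shown, may record the relevant times.

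Most of this stands, and it rules out the stronger reading that a reader might infer: that patients confirmed by their operation necessarily have M3 after treatment has begun or not at all, and that a quarter of confirmed cases are affected. The text says neither.

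The reply does not close the gap. Classing M3 as pre-treatment in the analysis states an intention but gives the person drawing the blood no rule. The abstract's wording has the same looseness about timing and conflicts with the empty cell in Table 1. The footnote describes a move made when the case is confirmed. Even if the columns are final categories, a site has to draw M3 before it knows which column will apply.

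Two further limits should be accepted. The IL-6 and D-lactate entries on reperfusion are animal data, and Table 2 does not mention surgical stress. A bias in the transmural versus non-transmural comparison through type of procedure is conceivable, but the documents give nothing from which to size it.

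**Conclusion.** The point holds as an inconsistency that puts samples at risk. The analysis section counts M3 as pre-treatment, while Table 1 and the Fig. 1 legend allow it to be drawn after the procedure has started. Read literally, Table 1 schedules no M3 for a patient who is still only suspected when the procedure begins; the abstract can be read to the contrary. A late or missing M3 is a possible result, not an established one.

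The size cannot be fixed from the article. The column gap affects between 0 and 40 NOMI patients plus an unknown number of occlusive cases first confirmed at surgery. The timing gap could affect any M3, in a share that is also unknown. This rests on the published article alone; site instructions or the case report form may already settle part of it. The matter deserves correction in the protocol, because the pooled cut-offs and the objectives rest on the pre-treatment label and the analysis cannot repair a mistimed draw.

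**What to change.** Reconcile the abstract, Table 1, the Fig. 1 legend and the Statistical analysis section on M3:

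- Define M3 as blood drawn immediately before the start of any procedure undertaken for suspected or confirmed AMI, and state which event counts as the start.
- Mark M3 in the suspicion column of Table 1, so that the draw does not wait for confirmation.
- Record the clock times of the draw, the start of the procedure and reperfusion, if the case report form does not already do so.
- Include M3 in the pooled pre-treatment set only when it was drawn before the start, and analyse later draws separately from that set.

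The change touches blood sampling only, which the protocol describes as its sole study procedure, and no treatment decision. The cost is one extra two-tube draw in the few suspected patients who have a procedure and are not confirmed. Their scheduled draws rise from four to at most five, below the six already possible for confirmed AMI with intervention. Some M3 values will also drop out of the pooled pre-treatment set because they were drawn too late.
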